#### **7.1.1. Clinical aspects of the acute and chronic phases of CD:**

Clinically, CD presents an acute phase, diagnosed in less than 10% of cases, due to the absence or presence of mild symptoms. The clinical course, in most cases, is towards spontaneous recovery (Berna, 2015), but without the elimination of parasites. The chronic phase may be asymptomatic (indeterminate), characterized by positive serology and some degree of cardiac involvement evidenced by minimal but persistent inflammation. However, after 10 to 30 years, in about 30% of patients, it progresses to symptomatic forms of the disease, with involvement of the esophagus, colon, or heart (Rassi et al., 2010). Physical symptoms and signs of chronic chagasic cardiomyopathy (CCC) arise from heart failure, cardiac arrhythmias (such as ventricular arrhythmias, atrioventricular block, supraventricular tachycardia, or atrial fibrillation) (Jefferies and Towbin, 2010) and arterial or venous thromboembolism (Rassi et al., 2017a).

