## **8. OBJECTIVE AND GOALS OF THE TRIAL**

### **8.1. Primary Goal:**

To evaluate the use of atorvastatin, in combination with antiparasitic therapy (NFX or BZD), is safe and more effective than antiparasitic therapy alone in preventing the occurrence of cardiac disturbances by reducing overall inflammation and in improving endothelial and cardiac functions.

To assess the primary endpoint, the number of patients with a change in the stage of chronic cardiomyopathy in 12 months from the beginning of antichagasic treatment will be considered.

We will evaluate whether the effect of atorvastatin in combination with antiparasitic treatment (NFX or BZD) is more effective than antiparasitic therapy alone (placebo group) in preventing the appearance of cardiac disorders determined by non-progression from stage A according to the First Latin American Guidelines for the diagnosis and treatment of chagasic cardiomyopathy (Andrade et al, Arq Bras Cardiol 2011;97 Suppl 3:1-48.) To make this assessment, significant changes in i) electrocardiogram (heart rate and QT interval duration, as well as the appearance of electrical conduction disorders, determined by QRS segment duration and morphology), ii) ejection fraction

(assessed by echocardiography), and iii) cardiac silhouette size (chest X-ray) will be taken into account

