## 9. Study design:

### 9.1. Outcomes:

As in any clinical trial, the results should be clearly defined beforehand. Thus, the **primary outcome** of this study at 12 months is the change in cardiac function in patients with chronic CAD. To this end, the number or proportion of patients presenting a change in the phase of chronic cardiomyopathy will be assessed. This phase change is determined by non-progression or reversion from or to phase A, according to the I Latin American Guidelines for the diagnosis and treatment of chagasic cardiomyopathy (Andrade et al., 2011), considering the consistent findings of structural alteration evidenced by changes in clinical, electrocardiographic, echocardiographic parameters and, additionally, of plasma levels of the cardiac function biomarkers BNP, cTnT.

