|                                                             | A                                                                                                                                       | B1                                                                                                                                                                                                           | B2                                                                                                                                               | C                                                                                                        | D                                                                                                                           |
| Patients with findings compatible with acute Chagas disease | Patients at risk for developing CHF. They have positive serology, neither structural cardiopathy nor CHF symptoms. No digestive changes | Patients with structural cardiopathy, evidenced by electrocardiographic or echocardiographic changes, but with normal global ventricular function and neither current nor previous signs and symptoms of CHF | Patients with structural cardiopathy characterized by global ventricular dysfunction, and neither current nor previous signs and symptoms of CHF | Patients with ventricular dysfunction and current or previous symptoms of CHF (NYHA FC I, II, III or IV) | Patients with refractory symptoms of CHF at rest, despite optimized clinical treatment, requiring specialized interventions |

Arq Bras Cardiol 2011; 97(2 supl.3): 1-48

The **secondary outcome** is determined by the change in plasma levels of biomarkers versus changes in parasite load.

Additional measures of scientific value: (a) change in plasma levels of biomarkers of inflammation and endothelial activation; (b) incidence and severity of AEs; (c) change in parasite burden and serologic response over the follow-up period, measured by quantitative PCR (qPCR); (d) changes in biomarker levels at different follow-up time points and correlation with parasite burden and ATO regimen; and (e) incidence of treatment discontinuation due to severe AEs.

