## 9.2. Statistical analysis: see section 11.

Clinical events related to CD occur at a low incidence in patients with the indeterminate CD due to the pathogenesis and hysteresis of the disease, parasite characteristics, and host response times; therefore, extensive clinical trials would be needed to assess changes in incidence. In addition, serologic and clinical endpoints of cure would require several years to decades in chronic CD (Bern, 2015). Consequently, the criterion of cure as a primary outcome, determined by seroreversion, is not considered in this proposal.

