Finally, a baseline resting ECG and a 2D echocardiogram will be performed. Both tests will be performed at each center. The ECG should be normal or with nonspecific changes (incomplete right bundle branch block, incomplete left anterior fascicular block, mild bradycardia, minor PR interval widening, and minor ST-T changes). Any clinically significant abnormality found on the electrocardiogram will automatically lead to the exclusion of the patient from this study (see exclusion criteria).

After randomization and before starting treatments, patients will undergo a new focused physical examination, and blood will be drawn for qPCR and biomarker determination.

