## 10. SELECTION AND WITHDRAWAL OF SUBJECTS

### 10.1. Inclusion criteria:

Subjects eligible to be enrolled in this trial must be adults older than 18 years and younger than 50 years, weighing more than 40 kg, with a conventional confirmatory serology for *T. cruzi* infection from the Instituto de Salud Pública de Chile (ISPCH). A positive qPCR will be selected to participate in this trial. Only patients with a new diagnosis of Chagas disease in the chronic indeterminate phase will be included. In addition, they must have normal values in laboratory tests for the following parameters: total white blood cell count, platelet count, creatine kinase (CK), alanine aminotransferase (ALT), aspartate aminotransferase (AST), total bilirubin or creatinine, or a gamma-glutamyl transferase (GGT)  $\leq 2$  times the upper limit of normal (X ULN); Women of reproductive age must have a negative serum pregnancy test, must not be breastfeeding, and must consistently use a highly effective method of contraception throughout the treatment phase.

Subjects must also meet all the following criteria: the ability to comply with all tests and follow-up visits specified in the protocol and have a permanent address; sign the written informed consent form.

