### 10.2. Exclusion criteria:

Signs and symptoms of the digestive form of CD; stage II or higher chronic cardiac CD; acute or chronic health conditions such as acute infections, history of HIV infection, diabetes, liver and kidney disease; pre-existing heart disease unrelated to Chagas disease; hypothyroidism, and family history of muscle disorders; formal contraindication to receiving NFX or BZD, known history of hypersensitivity, allergy or severe adverse reactions to ATO, BZD or NFX; history of prior treatment

for CD; history of previous treatment with atorvastatin, lovastatin, rosuvastatin, simvastatin or any other statin; any concomitant use of antimicrobial agents; history of alcohol or drug abuse; any condition that precludes oral medication; concomitant or intended use of CYP3A4 modifiers; a medical history of familial short QT syndrome or concomitant therapy with drugs that may shorten the QT interval. Abnormal laboratory test values for the following parameters: total white blood cell count, platelet count, creatine kinase (CK), alanine aminotransferase (ALT), aspartate aminotransferase (AST), total bilirubin or creatinine, or a gamma-glutamyl transferase (GGT) > 2 times the upper limit of normal (X ULN); Pregnant or lactating women; refusal to use a highly effective method of contraception during the treatment phase.

Patients meeting the selection criteria will undergo the randomization procedure. Only subjects enrolled in this trial will receive the study drugs. Patients will be assigned, in ascending order, a trial identification number (TIN) according to the enrollment order. A patient is considered randomized when s/he receives a TIN.

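### The primary outcome, change from stage A within 12 months, is badly underpowered and is not the outcome for which section 12.1 claims 90% power

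*Protocol*

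**What the plan says.** Section 8.1 bases the primary endpoint on the "number of patients with a change in the stage of chronic cardiomyopathy in 12 months", and section 9.1 adds: "This phase change is determined by non-progression or reversion from or to phase A". The scale is A to D, shown in Chart 1. Stage A is the indeterminate form: "They have positive serology, neither structural cardiopathy nor CHF symptoms". Stage B1 begins with an ECG or echocardiographic change while global function is still normal.

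On entry, section 10.1 states: "Only patients with a new diagnosis of Chagas disease in the chronic indeterminate phase will be included". Section 9.7 adds: "Any clinically significant abnormality found on the electrocardiogram will automatically lead to the exclusion of the patient". Section 10.2, however, excludes by name only "stage II or higher chronic cardiac CD", which belongs to the I-IV classification described in section 7.1.2.

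On natural history, section 7.1.1 says of the asymptomatic chronic phase that "after 10 to 30 years, in about 30% of patients, it progresses to symptomatic forms of the disease", counting oesophagus and colon as well as heart. Section 9.2 says clinical events are infrequent in indeterminate disease and that "extensive clinical trials would be needed to assess changes in incidence".

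Section 12.1 claims 90% power at 5% two-sided with 75 per group (100 after 25% dropout). It assumes that 0.40 on experimental treatment and 0.20 on placebo improve their ECG and echocardiographic parameters, BNP and cTnT at end of treatment. Section 12.4 names a one-sided Fisher test, but on a significant fall in biomarker levels. The Summary (efficacy analysis) adds that the two atorvastatin arms are merged if they do not differ significantly.

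**The concern.** A patient who starts at the best chronic stage has no better stage to reach. Reversion to A therefore contributes almost nothing, and the comparison depends on how many patients leave A within a year. The protocol itself describes that course as slow. If nearly everyone in every arm counts as a non-progressor, a useful effect of atorvastatin would most probably go undetected, and a null result could be misread as evidence of no effect on cardiac disease. The 90% power would also mislead readers, because it was worked out for a different quantity measured at a different time.

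**Working it through.** **1. The plan's own figure.** Inputs from section 12.1: p1 = 0.40, p2 = 0.20, 90% power, 5% two-sided.

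n = [1.96·√(2·0.30·0.70) + 1.2816·√(0.40·0.60 + 0.20·0.80)]² / 0.20² = (1.270 + 0.811)² / 0.04 ≈ 108.2, so 109 per group (119 with continuity correction).

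The stated 75 does not reproduce; at 75 per group two-sided power is 76.7%. The dropout step does: 75/(1 − 0.25) = 100. The shortfall is a separate matter. What counts here is which outcome the rates describe.

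**2. Do those rates fit the declared outcome?** They are proportions improving at end of treatment, whereas the outcome is stage at 12 months. Section 9.6 schedules echocardiograms only at screening and day 360. Read as improvement of stage, the attainable proportion is about zero in every arm. Read as non-progression, 0.20 on placebo would mean that 80% leave stage A within a year. Neither reading fits.

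**3. Annual progression rate from section 7.1.1.**
- Linear: 0.30/30 = 1.0% to 0.30/10 = 3.0%.
- Constant hazard: 1 − 0.70^(1/30) = 1.2% to 1 − 0.70^(1/10) = 3.5%.

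That is about 1 to 3.5 progressors per 100 placebo patients. The protocol gives no rate for silent A-to-B1 change; 5%, 10% and 20% below are assumptions.

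**4. Smallest significant result.** No test is named for stage change, so I apply the one-sided Fisher test of section 12.4 at 5%. With no progressor on atorvastatin:
- 100 vs 100, P = C(100,c)/C(200,c): 4 placebo events give 0.061 and 5 give 0.030, so 5 are needed.
- Pooled, 200 vs 100, P = C(100,c)/C(300,c): 2 events give 0.110 and 3 give 0.036, so 3 are needed.

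**5. Power by full enumeration of the Fisher test, no dropout.**

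| Placebo rate | Halved, 100 vs 100 | Halved, pooled 200 vs 100 | All prevented, 100 vs 100 | All prevented, pooled |
|---|---|---|---|---|
| 1% | 0.2% | 4% | 0.3% | 8% |
| 3% | 5% | 15% | 18% | 58% |
| 3.5% | 7% | 17% | 27% | 68% |
| 5% (assumed) | 12% | 21% | 56% | 88% |
| 10% (assumed) | 28% | 40% | 98% | over 99% |

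At an assumed 20%, a halving gives 57% pairwise and 70% pooled. With 75 evaluable per arm, a halving at 1-3.5% gives 0.1-4% pairwise and 2-13% pooled. Total prevention with pooling gives 39-49% at 3-3.5% and 73% at 5%.

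**6. Size needed.** Using the formula of step 1 for a halving from 3.5% to 1.75%:

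[1.96·√(2·0.02625·0.97375) + 1.2816·√(0.035·0.965 + 0.0175·0.9825)]² / 0.0175² ≈ 1,752 per arm.

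The same formula gives 6,256 at 1%, 1,212 at 5% and 582 at 10%.

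**The case against.** The best counter-argument is that 1-3.5% a year describes another transition. Section 7.1.1 counts symptomatic disease, whereas B1 needs only an ECG or echocardiographic change, and sections 8.1 and 9.1 also bring in QT, QRS, heart rate, cardiac silhouette, BNP and cTnT. Silent change could be more frequent. This stands, so the higher rates are labelled as assumptions. It does not rescue the power: a halving from 10% has 28% power pairwise and 40% pooled.

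A reader might infer that the trial cannot show a difference on this outcome, or that it will be null whatever atorvastatin does. The documents do not support that. Under the pooling rule in the Summary, 3 events against 0 are enough, and total prevention would be detected with 58-68% power at 3-3.5% and 88% at 5%.

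Nor does section 9.2 say that a trial of this size is too small. It says events are infrequent and large trials would be needed, and the only outcome it rejects is cure by seroreversion.

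Nor is stage A at entry guaranteed in every line. The inclusion criterion and Chart 1 imply it, but section 10.2 uses the other scale. A patient could also leave A and return by day 360. Such a patient would end where they began, so improvement on the entry stage remains essentially impossible.

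**Conclusion.** The point holds as a matter of power and of a mismatched power claim, not of impossibility. At the protocol's own progression figure, power to detect a halving is 0.2-7% for one dose against placebo and 4-17% with the doses pooled. Within that range of rates, only near-total prevention combined with pooling gives better than even odds. The 90% in section 12.1 does not carry over to stage change.

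This rests on three assumptions: stage A at entry, the one-sided 5% Fisher test applied to stage, and no dropout. The last two are generous to the plan. The main uncertainty is the A-to-B1 rate, which the protocol does not give. The outcome needs changing before the trial can support its main claim.

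**What to change.** - **Stage.** Make progression from A to B1 or beyond at day 360 a descriptive secondary outcome, with exact confidence intervals per arm. Drop reversion to A from the definition.
- **Entry.** Reconcile the stage II wording in section 10.2 with section 10.1 and Chart 1, so that entry and outcome use the same scale.
- **Power statement.** Say in section 12.1 that the 90% figure does not apply to stage change.
- **Primary.** Name one cardiac biomarker already collected and analyse it as a continuous, baseline-adjusted change. This moves in the direction of section 12.4, which already tests biomarkers. Log BNP is one candidate; section 9.6 schedules it at days 0, 60, 120 and 360. The protocol offers no SD or effect size for it, and levels in stage A patients may leave little room to fall. The sample size must therefore be justified afresh, with the assumed SD and effect shown.

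No new visit or procedure is needed. The costs are a recalculated section 12.1, which may not return 300 patients, a reworded objective and hypothesis, and a primary claim about a surrogate rather than about preventing cardiac disorders.

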**Chart 1 – Clinical classification of left ventricular dysfunction in chagasic cardiopathy**

| Acute phase                                                 | Chronic phase                                                                                                                           |                                                                                                                                                                                                              |                                                                                                                                                  |                                                                                                          |                                                                                                                             |
|-------------------------------------------------------------|-----------------------------------------------------------------------------------------------------------------------------------------|--------------------------------------------------------------------------------------------------------------------------------------------------------------------------------------------------------------|--------------------------------------------------------------------------------------------------------------------------------------------------|----------------------------------------------------------------------------------------------------------|-----------------------------------------------------------------------------------------------------------------------------|
|                                                             | Indeterminate form                                                                                                                      | Cardiac form with no ventricular dysfunction                                                                                                                                                                 | Cardiac form with ventricular dysfunction                                                                                                        |                                                                                                          |                                                                                                                             |
|                                                             | A                                                                                                                                       | B1                                                                                                                                                                                                           | B2                                                                                                                                               | C                                                                                                        | D                                                                                                                           |
| Patients with findings compatible with acute Chagas disease | Patients at risk for developing CHF. They have positive serology, neither structural cardiopathy nor CHF symptoms. No digestive changes | Patients with structural cardiopathy, evidenced by electrocardiographic or echocardiographic changes, but with normal global ventricular function and neither current nor previous signs and symptoms of CHF | Patients with structural cardiopathy characterized by global ventricular dysfunction, and neither current nor previous signs and symptoms of CHF | Patients with ventricular dysfunction and current or previous symptoms of CHF (NYHA FC I, II, III or IV) | Patients with refractory symptoms of CHF at rest, despite optimized clinical treatment, requiring specialized interventions |

Arq Bras Cardiol 2011; 97(2 supl.3): 1-48

The **secondary outcome** is determined by the change in plasma levels of biomarkers versus changes in parasite load.

Additional measures of scientific value: (a) change in plasma levels of biomarkers of inflammation and endothelial activation; (b) incidence and severity of AEs; (c) change in parasite burden and serologic response over the follow-up period, measured by quantitative PCR (qPCR); (d) changes in biomarker levels at different follow-up time points and correlation with parasite burden and ATO regimen; and (e) incidence of treatment discontinuation due to severe AEs.

## 9.2. Statistical analysis: see section 11.

Clinical events related to CD occur at a low incidence in patients with the indeterminate CD due to the pathogenesis and hysteresis of the disease, parasite characteristics, and host response times; therefore, extensive clinical trials would be needed to assess changes in incidence. In addition, serologic and clinical endpoints of cure would require several years to decades in chronic CD (Bern, 2015). Consequently, the criterion of cure as a primary outcome, determined by seroreversion, is not considered in this proposal.

## 9.3. Study description:

This is a proof-of-concept Phase II clinical trial with three different groups: Two groups will receive antichagasic therapy plus 40 or 80 mg/day of ATO. The third group will receive a placebo plus antichagasic therapy. The placebo is justified as long as the patient receives the complete conventional antichagasic treatment; therefore, the management of his Chagas disease is assured. In this clinical trial, the placebo will be a nutritional supplement tablet with an appearance similar to that of ATO. This product was chosen given the potential difficulties in manufacturing a small number of pills since the trial does not have a pharmaceutical industry sponsor capable of manufacturing it under Good Manufacturing Practice standards.

Nutritional supplements do not affect vascular or cardiac inflammatory parameters and therefore do not introduce confounding elements in the comparative analysis with atorvastatin.

Patients will first receive conventional antichagasic therapy for two months. After two weeks (or until normalization of liver enzymes), treatment with atorvastatin or placebo will be initiated for

four months. These doses were chosen to minimize false negative results, thus providing the best hypothesis test and maximizing the pharmacodynamic effect on inflammation and cardiac and endothelial function. In addition, the treatment sequence aims to minimize adverse reactions that could be caused by the eventual combination of antichagasic drugs with atorvastatin. Study subjects will be randomized, and the three groups will be double-blinded (both clinical investigators and subjects will be blinded) to ATO or placebo. However, antichagasic therapy will be open-labeled. In addition, qPCR and the other laboratory evaluations, as well as ECGs and 2D echocardiograms, will be performed with the clinical investigators blinded to ATO or placebo allocation.

This study will be conducted in four centers: 1) Hospital San Juan de Dios and 2) Hospital Felix Bulnes in Santiago, Metropolitan Region, 3) Hospital [name] in Viña del Mar, 4) Hospital San Martin de Quillota, Valparaiso Region. Each center annually admits 60 new patients to its Chagas Control Program (CCP). These four centers are part of the care network of the National Chagas Disease Control Program.

